### Monitoring study implementation

Three clinical psychologists, members of the study team, screen for the risk of unintended effects or harm to the participants (i.e., clinically significant increase in depressive symptomatology as measured by the CESD-R). Every participant’s CESD-R score is assessed weekly and interpreted clinically by the clinician assigned to them. If the participant does not complete the CESD-R assessment, the clinician will address this issue during the phone check-in. If necessary, the therapist can recommend the interruption of the participant’s access to the application.

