##### Exclusion criteria

Participants undergoing therapy (i.e., medication and/or psychotherapy), or presenting substance abuse problems, psychotic symptoms, organic brain disorders (e.g., dementia), self-injury or harming others, or serious health issues that would prevent from using the app, as well as participants reporting scores greater than 1 to question 9 (suicidal ideation) on the PHQ-9 [34] are excluded.

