### Therapist check-in

Three clinical psychologists provide all clinical contact with the active and placebo intervention participants, via phone calls. Every call is audiorecorded with the participant’s consent. The total therapist time spent per participant is also recorded. The therapists are instructed to limit contact time to approximately 5 min per participant, unless more time is clinically indicated. The therapist check-in component has the role of monitoring app use and mood status, without engaging in therapy, but encouraging intervention adherence.

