**Fig. 5 Fig5:**
[figure not shown]
Schedule of enrolment, interventions, and assessments

The participants in the active intervention and active placebo conditions are assessed at preintervention (time 1 – baseline), at mid-intervention (time 2 – 3 weeks after baseline), at post intervention (time 3 – 6 weeks after baseline), and at 3 months post intervention (time 4). The participants in the delayed-intervention condition are assessed before the waiting period (time 1 – baseline), at mid-waiting period (time 2 – 3 weeks after baseline), and at post waiting period (time 3 – 6 weeks after baseline).

Participants assigned to the active intervention condition will be given access to the online application along with explicit instructions regarding the use of all its sections. Participants will be given 6 weeks to complete the intervention, during which time weekly messages will be sent out to them. Messages include regular assignments designed for a complete and thorough use of the application’s courses and exercises, and encourage the review of materials whenever possible. However, participants are free to use the application at their own pace.

Similarly, the participants in the active placebo condition will be given access to a sham version of the app. During the 6-week intervention period they will be exposed to the same amount of online (i.e., in-app messages) and therapist communication as the active intervention participants.

After each week, participants’ app use is evaluated (see the Application Use Scale described above). Similarly, after each week of using the app, the participants are required to complete the CESD-R to monitor their depressive symptomatology and provide individualized in-app feedback on their emotional state.

The participants in the delayed-intervention condition are placed on a wait-list for 6 weeks, after which time they are given full access to the app.

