### Data collection, management, and analyses

#### Data collection methods

The initial assessment data are collected via the project website. Afterwards, a research assistant conducts telephone-screening interviews with potential participants to determine eligibility, and provides clinical screening reports. All subsequent assessment data are collected within the application, in the Evaluation section, and transferred to our servers using an encrypted, secure (https) industry-standard transfer protocol.

As far as participant retention and follow-up completion are concerned, the therapist check-in component of both the active and placebo interventions will play an important role. Besides being reminded of the specific assessment that needs to be completed after each intervention module, through the Messages section, the participants will also be encouraged by their assigned therapist to complete the assessments. Also, the therapist informs them that the weekly completion of the mood questionnaires allows the app to create a personalized profile of their mood, along with individualized visual feedback on their emotional state. Moreover, they are rewarded with more Energy after completing every assessment. Finally, for the follow-up assessments, the participants will receive new messages reminding them that free use of the app was possible because of a research grant, and thus data collection is essential. Additionally, participants are informed that they can attend an online psychological assessment with a clinical psychologist, based on the completion of follow-up questionnaires, if they wish to do so.

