### Ethics and dissemination

The Ethics Commission at Babeș-Bolyai University has approved this study. Although the intervention that it delivers cannot be considered a treatment for depressed people, it does target individuals with moderate depressive symptomatology who may be at risk for developing more severe depressive symptomatology. The screening process and the exclusionary criteria identify people who may be at risk for suicide. These people are immediately referred to the appropriate clinical services. If, during the use of the application, a participant’s condition worsens, the assigned clinician can recommend the interruption of that user’s access to the application. The project supervisor can further decide on such matters and, if necessary, make a further referral or recommendation. As far as data confidentiality is concerned, special efforts were made to secure the data online collection and storage. Both data collection means (i.e., via web browser of the mobile app) communicate with the server over industry-standard secure connections (i.e., https). The server stores the data in a password-protected database that is not publicly accessible. The system running our applications is kept up to date to prevent intrusions. Access to the electronic data is password-protected and only available to the project team of researchers and programmers. The passwords are changed regularly. The clinical screening reports contain no personal identifying information.

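### The weekly, clinician-read CESD-R promised for every participant fits only the two app arms; the wait-list has scores at weeks 3 and 6 and no workable step if someone worsens

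*Protocol article*

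**What the plan says.** The section Monitoring study implementation opens by giving three clinical psychologists on the study team the task of screening for harm, defined as a clinically significant rise in the CESD-R. It then sets out how: "Every participant’s CESD-R score is assessed weekly and interpreted clinically by the clinician assigned to them". If a form is missed, "the clinician will address this issue during the phone check-in". If needed, the therapist can recommend that access to the app be stopped.

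Other sections fix who receives these elements:

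- **Participant timeline** (text after Fig. 5): the weekly form is linked to app use, since "after each week of using the app, the participants are required to complete the CESD-R". The wait-list is assessed at baseline, then "at mid-waiting period (time 2 – 3 weeks after baseline), and at post waiting period (time 3 – 6 weeks after baseline", and receives the app only after the six weeks.
- **Therapist check-in**: "Three clinical psychologists provide all clinical contact with the active and placebo intervention participants, via phone calls". The section Data collection methods likewise describes the check-in as part of the active and placebo interventions.
- **Ethics and dissemination**: if, "during the use of the application, a participant’s condition worsens, the assigned clinician can recommend the interruption" of that user's access. The project supervisor's power to decide further and refer follows from that step.
- **Exclusion criteria**: people in therapy are excluded, as are those with "scores greater than 1 to question 9 (suicidal ideation) on the PHQ-9".

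**The concern.** The monitoring sentence is a safety statement about all three arms, and the protocol's own schedule does not bear it out for one of them. A reader judging participant protection would take it that untreated participants on the wait-list are reviewed weekly by a clinician who can act.

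These participants enter with PHQ-9 scores of 10 to 16 and are not in therapy at entry. The numerical cut-off on the PHQ-9 suicidal ideation item allows a score of 1. The Ethics section itself describes the target group as possibly at risk of more severe symptoms. What is at stake is that a worsening during the wait is seen late, or is seen and has no stated consequence.

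**Working it through.** The plan gives no count of monitoring scores, so there is no figure of its own to reproduce. The check sets the rule against the other sections, then counts.

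**Step 1: the rule, element by element**

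| Element of the monitoring rule | Active and placebo arms | Wait-list, first 6 weeks |
|---|---|---|
| CESD-R every week | Yes, after each week of app use | No: weeks 3 and 6 after baseline |
| Read by an assigned clinician | Supported: the psychologists provide the contact | None described |
| Missed form raised at phone check-in | Yes | No check-in described |
| Worsening: stop app access | Possible | Nothing to stop |
| Worsening: supervisor decision or referral (Ethics and dissemination) | Follows from worsening during app use | Not covered as worded |

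**Step 2: inputs for the count**

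- Recruitment target: 220 (Sample size).
- Three arms with simple randomization; participants are told of a 1 in 3 chance of placebo (Trial design, Assignment to study group). Equal allocation is taken from this.
- Waiting period: 6 weeks. A weekly rule therefore gives 6 post-baseline scores per person; the wait-list schedule gives 2.

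**Step 3: results**

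- Expected wait-list size: 220/3 = 73.3. Under simple randomization the 95% binomial range is 60 to 87.
- Scores implied by the rule: 73.3 × 6 = 440.
- Scores scheduled: 73.3 × 2 = 146.7, about 147.
- Difference: 440 − 146.7 = 293.3, which is 293.3/440 = 66.7% of the implied scores.
- At the ends of the size range the difference is 60 × 4 = 240 and 87 × 4 = 348.

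**Step 4: time to the next score**

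- Longest gap: 21 days on the wait-list schedule against 7 days under the rule.
- If a worsening starts at a uniformly random time and shows at the next score (assumption), the mean delay is 21/2 = 10.5 days against 7/2 = 3.5 days. This is delay to a score existing; the text sets no time for reading a wait-list score.

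**The case against.** The best defence is that the sentence is loosely worded. An assigned clinician, a phone check-in and stopping app access are all terms that belong to app users, and the timeline says outright that the weekly form follows app use. On that reading there was never a promise of weekly scores to the wait-list, and the 293 missing scores measure only the wording. Three-weekly assessment of a six-week wait-list is also a legitimate design choice. This much stands. It does not settle the matter, because on that reading the responses to worsening are confined to app users too, and the third arm is left with scheduled scores and no step that follows from them.

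The screening context also deserves weight. The Abstract says that people reporting suicidal ideation are excluded, a psychologist's interview is part of eligibility, and those found at risk at screening are referred at once. Being out of therapy is an entry criterion; nothing shown stops a wait-list participant from seeking care. These points lower the risk at entry but do not deal with worsening afterwards.

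Fig. 5 is not shown and the article condenses a fuller protocol, so further wait-list procedures may exist. The point therefore rests on what the article states too broadly, not on what it leaves out.

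Four stronger readings are tempting and are not supported:

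- **Nobody is responsible for wait-list scores.** The monitoring section opens with three psychologists screening participants without limiting this by arm, and a research assistant monitors assessments (Assignment to study group). The gap is the route from a score to an action, not the absence of any role.
- **The wait-list is stated to have no clinician.** No sentence says so. It is inferred from contact being described for the other two arms only.
- **Wait-list scores cannot be collected**, since "All subsequent assessment data are collected within the application, in the Evaluation section". The Ethics section also mentions a web browser, and it is full access that the wait-list receives after six weeks. The login route is a detail that an article may leave out.
- **Harm rates will be biased between arms by unequal numbers of scores.** No comparison of worsening rates across arms is planned in the text.

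**Conclusion.** The point holds as a mismatch between a stated safety procedure and the design of one arm. As worded, the weekly, clinician-read CESD-R is untrue for an expected 73 of 220 participants. They have two post-baseline scores in six weeks, no described clinician contact, and no applicable response to worsening. Reading the sentence as meaning app users corrects the wording but leaves that last gap open.

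The conclusion rests on equal allocation, on the timeline text being the complete wait-list schedule, and on the inference about clinician contact noted above. It concerns the waiting period only, since the wait-list gets the app afterwards. The efficacy contrasts are unaffected: the app and placebo arms share the same weekly monitoring, and the wait-list is still assessed at weeks 3 and 6. It should be corrected because it bears on participant safety and is cheap to put right; it does not threaten the trial's main inference.

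**What to change.** 1. In Monitoring study implementation, limit the weekly CESD-R read by the assigned clinician, and the check-in for missed forms, to the active and placebo arms.
2. State there that one of the existing study psychologists promptly reads the wait-list's week 3 and week 6 CESD-R, including the suicidal ideation items.
3. In Ethics and dissemination, word the worsening and referral step so that it covers all arms, not only worsening during app use.

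Do not add weekly calls or weekly forms to the wait-list, since that would change the control condition.

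The cost is two wording changes and psychologist review of about 147 scores that are already scheduled (73.3 × 2). The sample size, the assessment schedule and the app and placebo arms stay as they are, so the change can be made after recruitment has begun.

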### Ethics and dissemination

The Ethics Commission at Babeș-Bolyai University has approved this study. Although the intervention that it delivers cannot be considered a treatment for depressed people, it does target individuals with moderate depressive symptomatology who may be at risk for developing more severe depressive symptomatology. The screening process and the exclusionary criteria identify people who may be at risk for suicide. These people are immediately referred to the appropriate clinical services. If, during the use of the application, a participant’s condition worsens, the assigned clinician can recommend the interruption of that user’s access to the application. The project supervisor can further decide on such matters and, if necessary, make a further referral or recommendation. As far as data confidentiality is concerned, special efforts were made to secure the data online collection and storage. Both data collection means (i.e., via web browser of the mobile app) communicate with the server over industry-standard secure connections (i.e., https). The server stores the data in a password-protected database that is not publicly accessible. The system running our applications is kept up to date to prevent intrusions. Access to the electronic data is password-protected and only available to the project team of researchers and programmers. The passwords are changed regularly. The clinical screening reports contain no personal identifying information.

### Dissemination policy

Information on the development of the application and its clinical relevance has been presented at several international and national conferences. A first exploratory study protocol on the efficacy of the app in reducing cognitive vulnerability and mild depressive symptoms has already been published [36]. More information regarding research progress and dissemination can be found at the project’s designated website [60]. This trial’s results will be submitted for publication in a peer-reviewed journal, focusing on primary and secondary outcomes results.

## Discussion

This study describes a randomized clinical trial testing a smartphone app aimed at reducing moderate depressive symptoms. The target of this trial represents people with moderate depressive symptomatology. As there is no current clear evidence about the efficacy of smartphone apps in reducing depressive symptomatology, despite some preliminary studies that have shown promising results [19–24], this research can contribute substantially to clarifying the therapeutic merits of mobile interventions.

This study’s main aim is to test a newly developed app based on the CBT theory of depression to determine primarily whether this app is clinically useful in decreasing moderate depressive symptoms when compared with an active placebo. To our knowledge, this is the first attempt to test the efficacy of a smartphone app for depressive symptomatology in the form of an RCT that includes an active placebo condition. As such, this can substantially add to the body of evidence supporting the use of apps designed to decrease depression.

Additionally, this study investigates the app’s potential to contribute to the reduction of general negative affect, increasing positive affect, boosting satisfaction with life, and modifying depressogenic cognitions.

### Trial status

Participant recruitment has begun on 15 February 2017. Randomization of the participants was performed on the same day.

## Abbreviations

ATQ: Automatic Thoughts Questionnaire
BADS-SF: Behavioral Activation for Depression Scale–Short Form
BS: Beliefs Scale
CBT: Cognitive behavioral therapy
CESD-R: Center for Epidemiologic Studies Depression Scale–Revised
DAS: Dysfunctional Attitudes Scale
DAS-SF: Dysfunctional Attitudes Scale–Short Form
DSM-IV-TR: *Diagnostic and Statistical Manual of Mental Disorders, Fourth Edition, Text Revision*
GDB: Global Disease Burden
PANAS: Positive and Negative Affect Scale
PHQ-9: Patient Health Questionnaire, 9-item version
REBT: Rational Emotive Behavior Therapy
SWL: Satisfaction with Life
WHO: World Health Organization
